# Effectiveness and cost-effectiveness of routine third trimester ultrasound screening for intrauterine growth restriction: study protocol of a nationwide stepped wedge cluster-randomized trial in The Netherlands (The IRIS Study)

**DOI:** 10.1186/s12884-016-1104-8

**Published:** 2016-10-13

**Keywords:** Intrauterine growth retardation, Perinatal outcome, Midwifery, Third trimester ultrasonography

## Abstract

**Background:**

Intrauterine growth retardation (IUGR) is a major risk factor for perinatal mortality and morbidity. Thus, there is a compelling need to introduce sensitive measures to detect IUGR fetuses. Routine third trimester ultrasonography is increasingly used to detect IUGR. However, we lack evidence for its clinical effectiveness and cost-effectiveness and information on ethical considerations of additional third trimester ultrasonography. This nationwide stepped wedge cluster-randomized trial examines the (cost-)effectiveness of routine third trimester ultrasonography in reducing severe adverse perinatal outcome through subsequent protocolized management.

**Methods:**

For this trial, 15,000 women with a singleton pregnancy receiving care in 60 participating primary care midwifery practices will be included at 22 weeks of gestation. In the intervention (*n* = 7,500) and control group (*n* = 7,500) fetal growth will be monitored by serial fundal height assessments. All practices will start offering the control condition (ultrasonography based on medical indication). Every three months, 20 practices will be randomized to the intervention condition, i.e. apart from ultrasonography if indicated, two routine ultrasound examinations will be performed (at 28–30 weeks and 34–36 weeks). If IUGR is suspected, both groups will receive subsequent clinical management as described in the IRIS study protocol that will be developed before the start of the trial.

The primary dichotomous clinical composite outcome is ‘severe adverse perinatal outcome’ up to 7 days after birth, including: perinatal death; Apgar score <4 at 5 minutes after birth; impaired consciousness; need for assisted ventilation for more than 24 h; asphyxia; septicemia; meningitis; bronchopulmonary dysplasia; intraventricular hemorrhage; cystic periventricular leukomalacia; neonatal seizures or necrotizing enterocolitis. For the economic evaluation, costs will be measured from a societal perspective. Quality of life will be measured using the EQ-5D-5 L to enable calculation of QALYs. Cost-effectiveness and cost-utility analyses will be performed. In a qualitative sub-study (using diary notes from 32 women for 9 months, at least 10 individual interviews and 2 focus group studies) we will explore ethical considerations of additional ultrasonography and how to deal with them.

**Discussion:**

The results of this trial will assist healthcare providers and policymakers in making an evidence-based decision about whether or not introducing routine third trimester ultrasonography.

**Trial registration:**

NTR4367, 21 March 2014.

## Background

Monitoring fetal growth and well-being is a major objective of prenatal care [1]. Intrauterine growth retardation has often been defined as failing to achieve a specific fetal biometric or estimated fetal weight threshold by a specific gestational age [2]. IUGR is a risk factor for adverse outcomes, including perinatal death, neonatal encephalopathy, neurodevelopmental impairments in childhood, and disease in adult life [3–6]. To be able to provide timely clinical management for these fetuses, sensitive screening procedures for the detection of IUGR are needed. In many Western countries, including the Netherlands, primary midwifery and/or obstetric care mainly consist of serial fundal height assessments to monitor fetal growth patterns. Yet, this approach is not very effective as it only detects about one fifth or fewer neonates being small-for-gestational-age (birth weight <10th percentile by gestational age) [7–9], which is troublesome as being small-for-gestational-age (SGA) is a common finding among perinatal deaths [10, 11].

An alternative approach to detect IUGR fetuses comprises routine third trimester ultrasonography. A recent prospective cohort study (*n* = 3977) demonstrated that routine third trimester ultrasonography using estimated fetal weight or abdominal circumference approximately almost tripled the detection rate of SGA neonates (sensitivity = 57 %) [12]. Routine third trimester ultrasound screening may have other benefits, including the detection of structural fetal abnormalities, e.g. craniospinal abnormalities and urinary tract abnormalities, which become manifest late in pregnancy [13]. However, a meta-analysis of 13 randomized trials among low-risk pregnancies (*n* = 34,980) did not reveal beneficial effects of third trimester ultrasound screening on primary outcomes of perinatal mortality, preterm birth less than 37 weeks, Caesarean section rates, and induction of labor rates [14]. Two major shortcomings have been identified in these previous trials [14, 15]. First, previous trials had methodological shortcomings, e.g., most trials were underpowered to detect clinically significant differences in severe perinatal outcomes, heterogeneity in number and timing of ultrasound scans, and contamination, i.e., ultrasound scans were often also conducted in the control group [14, 15]. Secondly, in many trials only the ultrasound screening procedure was described but not the use of subsequent management/intervention procedures when IUGR is suspected. If not coupled with an effective intervention, ultrasound screening alone cannot be clinically effective [12]. Moreover, ultrasound technology used in most previous trials is now outdated [14, 15]. Reviews on the effects of routine third trimester ultrasound screening on pregnancy and perinatal outcome concluded that a large-scale trial with adequate power is needed to address severe adverse perinatal outcomes and to examine long-term neurodevelopmental outcome in the offspring [14, 16].

Introducing a screening program can have negative consequences, such as unnecessary medical care [17]. Defining IUGR based on a certain cut-off, e.g., the lowest 10th percentile of estimated fetal weight, will probably not only lead to the detection of growth restricted fetuses but also to the classification of a group of ‘at risk fetuses’ who are constitutionally small and healthy. This may lead to unnecessary interventions, such as elective induction of delivery.

Moreover, additional third trimester ultrasonography may affect maternal emotions, either positively in that negative screening results may be reassuring, or negatively in that it may increase maternal emotional distress, i.e., anxiety or depressive symptoms. Women may experience higher levels of emotional distress, due to an (incorrect) indication of IUGR and be exposed to additional monitoring and obstetric interventions [18, 19]. Experiences of maternal emotional distress due to positive, unexpected or unclear findings based on fetal ultrasound screening may continue into the postpartum period, even when abnormal screening results have not been confirmed by subsequent examinations [20–22].

In the case of positive screening results routine third trimester ultrasonography may particularly be related to the experience of moral dilemmas by pregnant women and professionals performing ultrasonography. For example, parents may find this burdensome due to increased responsibility that comes with the fact that they have to choose for further examinations of the fetus (or not). Professionals may find it difficult how to decide how much and which information they should provide to women/parents and when to advice referral for further clinical management [20–23].

Despite the lack of evidence for its clinical effectiveness [14, 15], routine third trimester ultrasound screening is increasingly used in midwifery care in the Netherlands, which results in a considerable rise in health care costs. Few former studies evaluated the cost-effectiveness of ultrasound scans [24, 25]. Although costs of the ultrasound examination itself have previously been investigated, we know little about resulting costs (e.g., costs associated with subsequent counselling, follow-up examinations, and subsequent interventions). So far, only one previous trial, The Helsinki ultrasound trial, addressed this matter showing that one-stage second-trimester ultrasound screening is cost-effective in reducing perinatal mortality as compared to care as usual when taking all significant costs and effects into account [25]. Moreover, the cost-effectiveness of routine third-trimester ultrasound screening combined with serial fundal height measurements and clinically indicated ultrasonography as compared to care as usual (CAU), i.e. serial fundal height measurements and clinically indicated ultrasonography alone, has not been studied earlier.

In the Netherlands, at the moment no multi-disciplinary consensus exists concerning the screening for and clinical management of suspected IUGR. To be more specific, the current monodisciplinary Dutch guidelines of the Royal Organization of Midwifes in the Netherlands (KNOV) and of the Dutch Association of Obstetrics and Gynecology (NVOG) for IUGR detection or management have a different focus and do not fully align [26, 27]. This may lead to inconsistent approaches in the clinical management of suspected IUGR. Therefore, another key element of our study is the development of a consensus-based multidisciplinary protocol for the detection and subsequent management of suspected IUGR using a Delphi study.

### Research aims

The main aim of the (IUGR risk selection study) IRIS study is to assess the effectiveness and cost-effectiveness of routine third trimester ultrasound screening at 28–30 weeks and at 34–36 weeks of gestation in comparison with CAU in reducing severe adverse perinatal outcome among low-risk pregnant women through subsequent protocolized management. The research aims of the IRIS study are:To evaluate whether routine third trimester ultrasound screening combined with subsequent protocolized management reduces severe adverse perinatal outcome as compared to CAU and subsequent protocolized management.To evaluate whether routine third trimester ultrasound screening combined with subsequent protocolized management is cost-effective as compared to CAU and subsequent protocolized management.To develop a multidisciplinary consensus‐based protocol for the detection and management of IUGR and to study professionals’ adherence to the protocol.To examine whether routine third trimester ultrasound screening combined with subsequent protocolized management affects maternal prenatal and postnatal psychological functioning and infant neurodevelopment at age 6 and 24 months as compared to CAU and subsequent protocolized management.To examine ethical dilemmas concerning positive, unclear, and unexpected findings and incorrect indication ofIUGR and to explore what professionals and women recommend regarding the handling of these ethical dilemmas.

## Methods/design

### Study design

The IRIS study is a nationwide stepped wedge cluster-randomized trial among 15,000 low-risk pregnant women receiving care at 60 midwifery practices in the Netherlands. The intervention entails routine third trimester ultrasound screening combined with serial fundal height measurements and clinically indicated ultrasonography, while the control condition entails CAU (serial fundal height measurements and clinically indicated ultrasonography only). In 1500 pregnant women derived from the entire study population a survey will be conducted to assess societal costs, maternal psychological functioning, maternal quality of life, and infant neurodevelopment. The exact design of the survey will be described in more detail later on.

Two sub-studies will be conducted as part of the IRIS study. In sub-study A, a Delphi study will be conducted to develop a multidisciplinary consensus-based protocol for the detection and subsequent management of IUGR in the Netherlands. Sub-study B will address ethical considerations of additional/routine third trimester ultrasound screening. These sub-studies will be described in more detail later on.

### Participants/eligibility criteria of participating midwifery practices

Practices will be eligible if all midwives are willing to follow the postgraduate registration training in the guideline ‘detection of IUGR’ of the KNOV [26]. Inclusion criteria for ultrasonographers that perform ultrasounds for women in the IRIS study are: 1) they have successfully followed the e-learning training for fetal biometry of the national medical e-learning education programs for medical students and professionals in the Netherlands (www.medischonderwijs.nl); 2) they possess a certificate for ultrasound anomaly screening (‘SEO’ certificate’) or will be judged as adequate performers of ultrasonography (based on 4 cases) by an IRIS study sonographer; 3) they use ultrasound equipment according to the standards of the NVOG [27]. Some midwifery practices perform ultrasound in their own practice; others refer to an ultrasound center.

Inclusion criteria for pregnant women are 1) receiving care in the participating midwifery practice at 22 weeks of gestation, having a singleton pregnancy and having no major obstetric or medical risk factors; and 2) having a reliable estimated date of delivery based on a dating ultrasound scan in line with NVOG guidelines or based on the first day of the last menstrual period [27].

### Recruitment and randomization

Figure 1 shows the flow chart of the study design. Midwifery practices will be informed about the IRIS study and invited to participate in the study via our nationwide Delphi study (sub‐study A). Other methods to invite midwifery practices for participation will include attending meetings of regional maternity care networks and the postgraduate training about the KNOV guideline [26], articles in national professional journals, and social media. A researcher will visit interested midwifery practices to provide information about the IRIS study, check whether the practice fulfils the inclusion criteria, and ask the midwives to sign a contract to demonstrate their commitment to the study protocol.

**Fig. 1 Fig1:**
[figure not shown]
Flow chart study design

During the first consultation after the 20-weeks pregnancy ultrasound screening has been offered, eligible pregnant women will be given a trial information leaflet by their midwife. The midwife will obtain consent.

Midwifery practices will form the unit of randomization. Randomization per practice rather than per midwife or woman minimizes contamination and maximizes contrast between the intervention and control group. As shown in Fig. 2, all midwifery practices (*n* = 60) will start in the control group. At 3 months intervals, a third of the midwifery practices will change status from the control to the intervention condition. To balance the number of women in the two conditions, practices will be stratified before randomization in large and small practices, with the average practice size as cut‐off (250 women per year). A stratified computer‐generated random sequence will determine the order in which practices change from control to intervention status. Randomization will be conducted by an independent statistician at 3 and 6 months after the start of baseline data collection and the recruitment of the first participating women.

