### Measures

#### Baseline characteristics of pregnant women and midwifery practices

To assess comparability of study groups and predictors of outcome, data on baseline characteristics of participating midwifery practices and participating pregnant women will be collected. Baseline characteristics of midwifery practices will include number of midwives working in the practice, number of clients per year, proportion of nulliparous and multiparous women, and rate of referral to secondary/tertiary care. Maternal baseline characteristics will include ethnic background, maternal age, educational level, height and weight, smoking, alcohol use, drug use, and work status during pregnancy.

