#### Effectiveness analyses

First, we will compare baseline characteristics of women participating in the intervention and control group using independent t-tests and chi-square tests. Second, we will compare baseline characteristics of drop-outs and completers by using independent t-tests and chi-square tests. Third, we will perform multiple logistic multilevel regression analysis to test the possible effect of routine third trimester ultrasound screening on severe adverse perinatal outcome. This analysis will be adjusted for possible clustering of observations at the level of midwifery practices and medical/biological, demographic and life-style related confounders. In all analyses, we will use an intention-to-treat approach and set the level of significance at *p* < 0.05.

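### The stated adjustment set for the primary model does not name the practice-size stratum used in randomisation; adding it is a small, free improvement

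*Protocol article*

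**What the plan says.** Under Recruitment and randomization, the article states: "Midwifery practices will form the unit of randomization". It adds that "practices will be stratified before randomization in large and small practices", using the average practice size of 250 women per year as the cut-off. The purpose given is "To balance the number of women in the two conditions". A stratified "random sequence will determine the order in which practices change from control to intervention status", so every practice contributes women to both conditions.

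Under Effectiveness analyses, the primary analysis reads: "we will perform multiple logistic multilevel regression analysis". The adjustment set follows: "This analysis will be adjusted for possible clustering of observations at the level of midwifery practices and medical/biological, demographic and life-style related confounders". The stratum is not mentioned there, either as included or as excluded.

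The section on baseline characteristics lists "number of clients per year" among the practice-level data to be collected, partly in order to study what predicts outcome. The information that defines the stratum is therefore on file for each practice.

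**The concern.** A factor used to restrict the randomisation is normally carried into the primary model. Stratifying removes chance imbalance in that factor from the true sampling variation of the treatment estimate. If the factor is prognostic and the model ignores it, the model's standard error still allows for variation that the design has removed, so the test is somewhat too cautious.

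Here the article does more than stay silent on covariates. It gives the adjustment set by class, and those classes (medical/biological, demographic, life-style) describe women, whereas practice size describes the practice. An analyst who followed the sentence literally would leave the stratum out. At stake is a little efficiency and calibration, not the validity of the comparison.

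**Working it through.** **1. The plan's own figure.** With 1.54% against 1.0%, two-sided 5%, 80% power and equal groups, the pooled formula gives

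n per group = [1.96 × √(2 × 0.0127 × 0.9873) + 0.8416 × √(0.0154 × 0.9846 + 0.010 × 0.990)]² / 0.0054² ≈ 6,749,

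or 13,498 in all, within 0.3% of the stated 13,536. The design effect is 1 + 249 × 0.0003 = 1.0747, and 13,536 × 1.0747 = 14,547, as stated. No stratum term enters, so the point does not touch the sample size. Expected events: 7,500 × 0.0154 + 7,500 × 0.010 ≈ 190.

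**2. Does the practice random intercept replace the stratum?** Only partly. With 250/4 = 62.5 women per practice and period (equal practice sizes assumed) and ICC 0.0003, the ratio is 62.5 × 0.0003/0.9997 = 0.01876. The weight on a practice's own mean is 4 × 0.01876/(1 + 4 × 0.01876) = 7%. At ICC 0.002, the top of the cited range, it is 33%.

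**3. How far is the treatment contrast exposed to differences between practices?** Take 60 practices and 4 periods, with 20 practices switching at each step.

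- Total variation in treatment status: 240 × 0.25 = 60.
- Between practices (practice means 0.75, 0.50, 0.25): 4 × (20 × 0.0625 + 20 × 0.0625) = 10.
- Left after removing period means: 26.67, still with 10 between practices.

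So 10/60 = 17% of the variation lies between practices without period terms, and 10/26.67 = 37.5% with them. The rest is within practices, where a constant effect of practice size cancels.

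**4. What does leaving the stratum out cost?** A stepped-wedge simulation was run with 1,500 trials per setting. The switching order was randomised within strata, and generalised least squares on cell proportions was fitted with a random practice intercept and known variance components. Assumptions not in the documents: 30 small practices of 150 women, 30 large of 350, and the stratum risks below (each pair averages about 1.54% over women). The ICC was 0.0003 within strata. Because the article does not name a period term, both forms were run.

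| Risk small / large | Period term | Type I error, without / with stratum | Power, without / with stratum |
|---|---|---|---|
| 1.54% / 1.54% | no | 3.7% / 3.7% | 79.1% / 79.1% |
| 1.94% / 1.37% | no | 4.7% / 4.7% | 77.2% / 78.1% |
| 2.24% / 1.24% | no | 4.6% / 5.9% | 76.6% / 78.2% |
| 1.54% / 1.54% | yes | 5.1% / 5.1% | 43.3% / 43.3% |
| 1.94% / 1.37% | yes | 3.9% / 4.5% | 38.7% / 40.7% |
| 2.24% / 1.24% | yes | 3.8% / 4.7% | 37.9% / 44.1% |

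The Monte Carlo error of a type I error figure is about 0.6 points. Mean bias never exceeded 0.0001 in absolute value, on an effect of 0.0054, with or without the stratum. The lower power with a period term is a separate matter and does not depend on the stratum.

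**5. Reading the last row.** The 6.2-point gap is not mainly a gain in precision. The actual standard deviation of the estimate falls only from 0.00286 to 0.00281. Setting 0.0054 against these gives 1.888 and 1.922, hence powers of Φ(−0.072) = 47.1% and Φ(−0.038) = 48.5%, about 1.3 points apart. The remainder comes from the model standard error without the stratum (0.00323) being further above the truth than the one with it (0.00305).

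This setting is also extreme. With equal numbers of large and small practices, the size effect alone contributes 0.005²/(0.0154 × 0.9846) ≈ 0.0016 to the ICC. Adding 0.0003 brings it to about 0.0019, near the 0.002 that the protocol considers unlikely.

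**The case against.** The strongest reply is that the covariates are given only as broad classes in a condensed article, that nothing excludes practice size, and that an analysis plan not shown may list it. This stands in part: the text supports saying that the stratum is not named, not that it has been ruled out. It does not remove the point, because the classes given do not cover a practice-level factor.

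A second reply is that stratification was meant to balance numbers of women, not prognosis. That is true, but the draw is restricted by size whatever the motive.

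A third is that the premises pull against each other: an ICC near 0.0003 leaves little room for a size effect. With equal numbers of each, 1.94% against 1.37% alone gives 0.00285²/(0.0154 × 0.9846) ≈ 0.0005. This also stands, and it is why the expected gain is small.

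Three stronger readings are tempting, and none is supported:

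- A reader might infer that the analysis does not follow the randomised groups. The randomised units are practices, and the model clusters on them.
- A reader might take the stepped-wedge variance formula, with terms 1,600 and 75, to show that over 95% of the information lies between practices. The 1,600 is 60 × 26.67, the whole period-adjusted variation, of which only 10/26.67 is between practices.
- A reader might infer that imbalance in size biases the estimate. The order is drawn at random within strata, every practice gives both conditions, and the simulated bias was nil.

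**Conclusion.** The point holds as a minor one: randomisation is stratified by practice size, and the stated adjustment set neither names the stratum nor has a class that would contain it. Omission causes no bias and no type I error inflation (3.7% to 5.1% without the stratum). If risk differs by practice size, the test is slightly conservative and less efficient, by roughly 0 to 2 power points. The one larger nominal gap, 6.2 points, needs both a period term and an extreme assumed risk difference, and mostly reflects an over-wide standard error. If size carries no risk difference, the loss is zero.

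These figures rest on assumed practice sizes and stratum risks, a linear approximation to the logistic model and known variance components. They indicate the order of magnitude only.

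**What to change.** Name the randomisation stratum (large or small practice, cut-off 250 women per year) as a fixed effect in the primary multilevel logistic model and in the secondary models that compare the two conditions. Use the classification applied at randomisation, even if a practice's volume later changes. If the analysis plan already does this, a sentence in the protocol pointing to it is enough.

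The cost is one degree of freedom against about 190 events. No new data are needed and the sample size stays as it is. Fixing the term in advance also removes a choice that would otherwise be made after the data are seen.
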